### Power calculation

Based on a conservative estimate from the smallest hospital, we assume an average of 3,600 cases from each of the four hospitals in a 4-year period. Thus, we anticipate a total sample size of 14,400 cases over the study period. We assume that 30% of cases have an average trauma-to-CRI time within 2 h of injury and an average 7-day mortality of 10% for the primary mortality outcome. From a Cox proportional hazards regression, with 80% power (alpha = 0.05, two-sided) we can detect a hazard ratio of 0.85 for trauma-to-CRI time within the first 2 h versus not. For the morbidity outcomes, we present the power calculation for a continuous outcome (organ failure), and a binary outcome (wound infection). For the continuous outcome of organ failure, assuming the standard deviation of the SOFA score is 4 [71], with 80% power (alpha = 0.05) we can detect a mean decrease in score of 0.20 in those with trauma-to-CRI time within the first 2 h versus not, which corresponds to a standardized effect size of 0.05. For the binary outcome indicating whether a wound infection occurred, if 10% of cases with a trauma-to-CRI time within 2 h have a wound infection, with 80% power (alpha = 0.05, two-sided) we can detect an odds ratio of 0.84 for trauma-to-CRI time within 2 h versus not.

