### Missing data

Missingness of key measures will be minimized during the data collection process. The primary analysis will be a complete-case analysis that excludes observations that are missing key exposure, outcome, and predictor variables. Characteristics will be compared between those with and without complete data. Sensitivity analyses will be conducted using imputation methods for missing predictor values based on multiple imputation techniques [70].

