## Limitations

There are several limitations to this study design and methodology. First, the chart review and abstraction approach present challenges such as missing data and difficulty deciphering handwritten records. To mitigate this, the study will continuously monitor data completeness and provide ongoing feedback to data collectors. Second, EpiC data will be prone to selection bias as not all injured individuals seek medical attention, and because the study population is limited to those seeking care at specified facilities [76]. Additionally, EpiC does not collect information for individuals that die during non-EMS transport to the hospital, which will potentially exclude individuals with extremely severe injuries from our analysis and will limit the generalizability of results to this population. Further, EpiC began enrollment during the COVID-19 pandemic when trauma caseloads across South Africa and in the Western Cape Province were reduced by up to 50% [36], which can result in the reporting of rates that are lower compared to pre-COVID periods.

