## Trial status

To date, the preparatory work (phase 1: September 30, 2019 to December 31, 2020) and pilot study (phase 2: January 1, 2021 to August 30, 2021) of the EpiC study have been completed and informed the structure and conduct of the main phase (phase 3: began September 1, 2021) that is ongoing. Trained research personnel are currently collecting study data at all EpiC study sites in the Western Cape Province and will conclude data collection in September, 2024.

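### The 14,400 cases behind HR 0.85 at 80% power assume four years' accrual and no excluded cases; with about three years of main-phase collection and a complete-case primary analysis, that power is not shown to be attainable

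*Protocol article*

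**What the plan says.** **Sample size.** The Power calculation section opens with "Based on a conservative estimate from the smallest hospital" and continues "we assume an average of 3,600 cases from each of the four hospitals in a 4-year period". From this it concludes "we anticipate a total sample size of 14,400 cases over the study period".

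**Power inputs.** The same section assumes "30% of cases have an average trauma-to-CRI time within 2 h of injury", 7-day mortality of 10%, two-sided alpha of 0.05 and 80% power. It states a detectable hazard ratio of 0.85 for the primary outcome, a SOFA difference of 0.20 and a wound-infection odds ratio of 0.84. It makes no deduction for cases that cannot be analysed.

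**Dates.** Trial status gives "phase 3: began September 1, 2021" and says that the team "will conclude data collection in September, 2024". The pilot ran from January to the end of August 2021, and the Study design section sizes it at about 1,000 patients.

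**Analysis set.** The Missing data section says: "The primary analysis will be a complete-case analysis that excludes observations that are missing key exposure, outcome, and predictor variables". Limitations names missing data and hard-to-read handwritten records as challenges. No expected rate of missing data is given.

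**The concern.** The calculation needs 48 months of accrual at 300 cases a month (14,400 / 48), whereas the stated main-phase collection window is about 36 months. It also needs almost every enrolled case to be analysed, whereas the primary analysis removes any case with a missing key exposure, outcome or predictor. Both differences reduce the number of deaths analysed, and that number determines power in a Cox model.

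The interpretation of the primary result is at stake. A null finding on 7-day mortality would be read against 80% power for HR 0.85, when the number of deaths analysed may support noticeably less.

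**Working it through.** **Inputs (Power calculation section unless noted).** N = 14,400; 10% dead by day 7; 30% exposed and 70% not; two-sided alpha 0.05; 80% power. Accrual is 4 × 3,600 / 4 years = 3,600 per year overall. Window (Trial status): September 2021 to September 2024, about 3 years.

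**Formulas (Schoenfeld, unequal groups), with D = number of deaths.**
- Deaths needed: D = (1.960 + 0.842)² / (0.3 × 0.7 × (ln HR)²)
- Detectable HR = exp(−2.802 / √(0.21 × D))
- Power at HR 0.85 = Φ(√(0.21 × D) × |ln 0.85| − 1.960)

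**Step 1: reproduce the plan's figure.** D = 14,400 × 0.10 = 1,440. Detectable HR = 0.851 and power at 0.85 = 80.7%, so the stated figure reproduces. HR 0.85 at 80% power needs 1,416 deaths, or 14,160 analysed cases. The slack is (14,400 − 14,160) / 14,400 = 1.7%.

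**Step 2: the plan's rate over the stated window, with no exclusions.**

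| Basis | Cases | Deaths | Power at HR 0.85 | Detectable HR |
|---|---|---|---|---|
| Main phase, 3 years | 10,800 | 1,080 | 68.7% | 0.830 |
| Main phase plus about 1,000 pilot patients | 11,800 | 1,180 | 72.5% | 0.837 |
| January 2021 to September 2024 at full rate, 44 months | 13,200 | 1,320 | 77.2% | 0.845 |
| The same, 45 months | 13,500 | 1,350 | 78.1% | 0.847 |

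No reading of the dates reaches 80% at that rate.

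**Step 3: complete-case loss if all 14,400 are enrolled.** The document gives no rate, so these losses are assumed.

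| Assumed loss | Analysed | Power at HR 0.85 | Detectable HR |
|---|---|---|---|
| 5% | 13,680 | 78.7% | 0.848 |
| 10% | 12,960 | 76.5% | 0.844 |
| 20% | 11,520 | 71.5% | 0.835 |

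With both effects together (10,800 enrolled), an assumed 10% loss gives 64.1% power and a 20% loss gives 59.1%.

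**Step 4: accrual that would rescue the claim.** 14,160 / 3 = 4,720 complete cases per year, and 4,720 / 3,600 = 1.31. That is 31% above the assumed rate with nothing missing. With an assumed 10% loss it is 14,160 / 0.9 / 3 = 5,244 per year.

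**Step 5: morbidity figures.** For SOFA, the detectable difference is 2.802 × 4 × √(1/(0.3N) + 1/(0.7N)). This is 0.204 at 14,400 (stated 0.20), 0.215 at 12,960 (10% removed) and 0.235 at 10,800. For wound infection with a 10% rate in the early group, as the section words it, the detectable odds ratio is 0.850 at 14,400, 0.843 at 12,960 and 0.830 at 10,800. The stated 0.84 matches 14,400 if 10% is instead the rate in the later group (0.841). These shifts are small and secondary.

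**The case against.** **The rate is a floor.** The strongest reply is that 3,600 per hospital is called conservative and comes from the smallest site. Study setting gives the trauma centre alone 12,000 to 15,000 seriously injured persons a year, against the 900 per hospital per year assumed. Not all would be eligible, but a 31% higher rate is plausible. This stands: a reader might infer that 80% power will not be delivered, and the documents do not support that. They also do not claim the higher rate, and 3,600 per hospital is the only accrual figure the calculation uses.

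**The arithmetic is right.** This also stands. The fault lies in the inputs, which do not match the dates and the analysis set.

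**Phase 3 as years 3–6.** A reader might take this as a second error. It need not be: Phase 1 began on 30 September 2019, so year 3 starts about September 2021, and Phase 3 includes statistical analysis as well as collection. Only the 4-year accrual period conflicts with the dates.

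**Pilot patients may count.** The sample is described as accruing over the study period, so 69% is one reading and 77% to 78% another. The document does not say which applies.

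**COVID-19.** Limitations reports that "trauma caseloads across South Africa and in the Western Cape Province were reduced by up to 50" per cent. This weakens an assumption of faster accrual, but it concerns the time when enrolment began and no accrual figure can be derived from it.

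**Missing data and deaths.** The loss rates in step 3 are assumptions, and multiple imputation is already planned as a sensitivity analysis. For morbidity, removing every death is not established as right: SOFA is assessed up to day 7, so patients who die may contribute earlier values, and the plan weights for death. What remains is the 1.7% slack, which does not depend on the accrual question.

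**Conclusion.** The point holds in limited form. The document's accrual period and collection window disagree by about a year, and its power statement makes no allowance for a complete-case primary analysis. HR 0.85 at 80% power is therefore not shown to be attainable as planned.

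At the plan's own rate, power at HR 0.85 is 69% for the main phase alone and 73% to 78% with the pilot, before any exclusions. The detectable HR moves from 0.85 to 0.83 at the main-phase figure. These numbers rest on accrual staying at 3,600 a year, 10% mortality and 30% exposed. If 14,400 are enrolled after all, a complete-case loss above about 1.7% still takes power below 80%.

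This is an inconsistency in a figure on which the study relies. It does not show that the study will be underpowered, and it does not affect the validity of the planned analysis.

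**What to change.** - Reconcile the 4-year period in the Power calculation section with the collection dates in Trial status, and say whether pilot patients count towards the sample.
- Restate the expected number of complete cases from the accrual and missingness observed so far.
- Restate the power or detectable hazard ratio for that number. Restate the SOFA difference and the infection odds ratio for the number expected to contribute to each analysis, and make clear which group the 10% infection rate describes.

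No extra patients are needed, and the primary missing-data method can stay as it is. The cost is a short rewrite, and the stated figures may become slightly less favourable.

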## Discussion

Globally, the burden of trauma remains high, particularly in LMICs and military populations. Timely delivery of quality trauma care is critical to improving trauma outcomes. Trauma patterns and determinants of outcomes need to be well characterized, epidemiologically and clinically, to strengthen clinical care, trauma policies, and system-level processes. In high-income countries and the U.S. military, the introduction of trauma databases and registries has led to a significant reduction in post-injury death and disability. Yet, trauma registries are non-existent in most LMICs and where they do exist, in both civilian and military settings, there are a myriad of opportunities to supplement or improve the quality of existing data [4, 72–74].

The EpiC study represents the first effort to build a standardized, multicenter database of trauma in South Africa, beginning in the Western Cape. This DOD funded study will focus on trauma outcomes of critically injured civilians, many experiencing prolonged trauma-to-CRI times, in a resource-limited, high-trauma mortality setting. In the EpiC study, critical information on injuries is obtained, including predisposing and epidemiologic factors of trauma risk, care, treatment history, and patient outcomes. Findings from EpiC will help fill critical gaps in the scientific body of literature relevant to strengthening care of persons in the Western Cape, South Africa, other LMICs, and in the U.S. military combat-wounded.

Data from EpiC will also provide rich clinical information, absent from existing Western Cape hospital databases, which can be used to evaluate the efficacy of interventions, including the effects of delays and minimum interventions needed. The prehospital data in EpiC will uniquely include systems-level data on transport times and transfer patterns. This information will shed light on operational and controversial practices, including the benefits of bypassing nearby facilities in favor of busy trauma centers in resource-limited and rural settings. At the institutional and trauma system administrative level, findings from EpiC will help guide resource allocation, provide surveillance data that can be used for trauma quality improvement programs, describe the trauma population and care received, and inform institutional and government reports aimed at improving care and patient outcomes. From the combat casualty perspective, the EpiC study can contribute data which are needed to help plan U.S. military missions, casualty management risk mitigation strategies, and understand the likely effects of injuries in the setting of prolonged times before reaching an advanced resuscitative/surgical team or definitive care center [75].

## Limitations

There are several limitations to this study design and methodology. First, the chart review and abstraction approach present challenges such as missing data and difficulty deciphering handwritten records. To mitigate this, the study will continuously monitor data completeness and provide ongoing feedback to data collectors. Second, EpiC data will be prone to selection bias as not all injured individuals seek medical attention, and because the study population is limited to those seeking care at specified facilities [76]. Additionally, EpiC does not collect information for individuals that die during non-EMS transport to the hospital, which will potentially exclude individuals with extremely severe injuries from our analysis and will limit the generalizability of results to this population. Further, EpiC began enrollment during the COVID-19 pandemic when trauma caseloads across South Africa and in the Western Cape Province were reduced by up to 50% [36], which can result in the reporting of rates that are lower compared to pre-COVID periods.

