### Variables, outcomes, and study measures

Epidemiologic information will be collected for each study participant for their entire clinical course at all associated study sites, including: patient demographic information (e.g., age, sex, race, and comorbidities); injury details (e.g., time, type, and intent); facility data (e.g., hospital name, trauma level, clinician qualifications, units of care); clinical data (e.g., vital signs, medications administered, critical interventions, operations performed); and, trauma system process (e.g., key dates and times [51]). Table 2 describes the exposures, predictors, and outcomes of interest in the EpiC study.

**Table 2 Tab2:** Key EpiC Study Exposure, Predictors, and Outcome Measures

Exposures	Definition	Variable Type	Data Source
1^O—^Critical resuscitative interventions (CRI)	Prehospital and in-hospital resuscitative interventions or therapeutics, delivered for the patient’s traumatic injury (e.g., thoracostomy for tension pneumothorax), within the first 24 h post-injury	Binary	EMS and/or Hospital
1^O^—Trauma-to-CRI time	Duration of time from injury to receiving a critical resuscitative intervention for the dominant injury	Continuous	EMS, Hospital, and/or Pathology

Predictors	Definition	Variable Type	Data Source
Age	Span of years lived at the time of injury	Continuous	EMS, Hospital, or Pathology
Sex	Biological sex given at birth	Categorical	EMS, Hospital, or Pathology
Comorbidities	One or more pre-existing disease or conditions present in the patient that are trauma-relevant chronic conditions (e.g., bleeding disorder)	Binary	EMS or Hospital
Socioeconomic status	Based on hospital insurance status	Categorical	Hospital
Mechanism of injury	Main force that created the injury or how injury was inflicted (e.g., firearm, Struck/hit, stabbing or cut, vehicular injury, fall, thermal, choking/hanging, iatrogenic, other)	Categorical	EMS, Hospital, or Pathology
Provider level	Health care provider qualifications (e.g., rank of EMS provider, type of doctor)	Categorical	EMS
Injury severity	ISS calculated as the sum of squares of 3 worst AIS scores. Low (< 12) or high (≥ 12)	Continuous, Binary	EMS, Hospital, or Pathology

Outcomes	Definition	Variable Type	Data Source
1^O—^Ambulance death or 7-day in-hospital mortality	All-cause mortality in the ambulance or within the hospital in the first 7-days post-injury	Time-to-event	EMS, Hospital, or Pathology

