## Statistical methods

Descriptive statistics will be estimated for all demographic, injury, facility, clinical, and systems process fields. Multivariable models will adjust for characteristics at the patient-level (e.g., age, sex, race, comorbidities, socio-economic status, injury mechanism, injury severity index) and provider-level (e.g., specialist trauma surgeon, general medical officer, advanced prehospital provider), as described in Table 2. Due to the small number of hospitals, site will be adjusted for as a fixed effect.

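### The stated adjustment has no calendar-time term, although caseloads were down by up to half when enrolment began: a potential confounder of CRI timing and mortality that costs little to remove

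*Protocol article*

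**What the plan says.** Statistical methods sets out the adjustment in three parts.

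- Patient level: "Multivariable models will adjust for characteristics at the patient-level (e.g., age, sex, race, comorbidities, socio-economic status, injury mechanism, injury severity index".
- Provider level: "e.g., specialist trauma surgeon, general medical officer, advanced prehospital provider), as described in Table 2".
- Site: because there are few hospitals, "site will be adjusted for as a fixed effect".

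Neither this section nor the predictor block of Table 2 names year, quarter, pandemic phase or any other calendar term.

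The Limitations section says that enrolment began during the COVID-19 pandemic, when "trauma caseloads across South Africa and in the Western Cape Province were reduced by up to 50" per cent. It draws one consequence: "which can result in the reporting of rates that are lower compared to pre-COVID periods". It does not mention the CRI effect estimates.

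The Trial status section puts the pilot at January to August 2021 and the main study after it ("phase 3: began September 1, 2021"), with data collection ending in September 2024. The Background section on the EpiC study lists time trends in trauma epidemiology and care among the things the study will inform. Dates are recorded for every patient: the variables include "trauma system process (e.g., key dates and times".

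**The concern.** The main exposure is how quickly a CRI is delivered. The Background attributes delays in civilian settings mainly to slow prehospital response or transport and to long stays at a first hospital that is not a trauma centre. Such delays could plausibly change with the load on the system, and case mix and mortality could change too. If CRI timing and mortality both moved with calendar period, pooling several years without a period term would credit or charge some of that movement to early CRI.

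A site fixed effect does not prevent this. It removes stable differences between hospitals, not changes within a hospital over time. Severity and mechanism would absorb a shift in case mix only as far as they measure it. Bias of this kind also does not shrink as the sample grows. The article itself names a large period change and then leaves it out of the part of the analysis where it could matter most.

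**Working it through.** **1. The plan's own figure.** Inputs from Power calculation: 14,400 patients, 30% with CRI within 2 h, 7-day mortality 10%, two-sided alpha 0.05, power 80%, detectable hazard ratio (HR) 0.85.

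- Expected deaths: 14,400 × 0.10 = 1,440.
- Deaths needed (Schoenfeld): (1.960 + 0.842)² / [0.30 × 0.70 × (ln 0.85)²] = 7.849 / (0.21 × 0.02641) = 1,416, rounded up.
- Power with 1,440 deaths: Φ(√(1,440 × 0.21) × 0.1625 − 1.960) = Φ(0.866) = 80.7%.
- Detectable HR at 80% power: exp(−2.802 / 17.39) = 0.851.

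The stated 0.85 reproduces.

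**2. Assumptions.** The documents give no figure linking calendar period to CRI timing or to mortality, so ranges are assumed:

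- share of patients in the low-caseload period, w = 10-30%;
- excess share with early CRI in that period, d = 2-15 points, with 30% overall;
- mortality ratio, low-caseload period versus the rest, r = 0.8-1.25;
- no true effect of early CRI.

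**3. Bias without a period term.** The early-CRI share in the low-caseload period is p = 0.30 + d(1 − w). The fraction of early-CRI patients who come from that period is qE = w·p/0.30. For the others it is qL = w(1 − p)/0.70. The spurious ratio is [1 + qE(r − 1)] / [1 + qL(r − 1)].

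Worked corner, w = 0.30 and d = 0.15: p = 0.405, qE = 0.405, qL = 0.255. At r = 0.8 the ratio is 0.919/0.949 = 0.968. At r = 1.25 it is 1.10125/1.06375 = 1.035.

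**4. Power after adding the term.** Effective deaths are 1,440 × (1 − R²), where R² = w(1 − w)d²/0.21 is the share of variance in early CRI explained by a two-level period.

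| w | d | Ratio, r = 0.8 | Ratio, r = 1.25 | R² | Power for HR 0.85 |
|---|---|---|---|---|---|
| 0.10 | 0.05 | 0.996 | 1.005 | 0.0011 | 80.6% |
| 0.10 | 0.15 | 0.987 | 1.016 | 0.0096 | 80.3% |
| 0.20 | 0.05 | 0.992 | 1.009 | 0.0019 | 80.6% |
| 0.20 | 0.15 | 0.976 | 1.027 | 0.0171 | 80.0% |
| 0.30 | 0.05 | 0.989 | 1.012 | 0.0025 | 80.6% |
| 0.30 | 0.15 | 0.968 | 1.035 | 0.0225 | 79.8% |

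Over the whole grid, power stays at 79.8-80.7% and the detectable HR at 0.850-0.851.

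**5. Scale.** The standard error of the log HR is 1/√302.4 = 0.0575. The extreme ratios, 0.968 and 1.035, are 0.56 and 0.60 standard errors from no effect. They would raise a 5% two-sided false-positive rate to about 9%. With w = 0.30 and d = 0.05 the rate is about 5.5%.

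These are crude risk ratios, used as an approximation to the HR. Whatever the planned adjustment for severity, mechanism, provider and site absorbs would reduce them.

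**The case against.** The strongest reply is that nothing here is wrong on its face. Both covariate lists are illustrative. The text names race, which is not among the Table 2 predictors, so Table 2 is not a closed list either. The article condenses a fuller protocol, and a statistical analysis plan that is not shown may contain a period term. This stands in part: the article does not rule out calendar time. But the lists are open only within their classes, and calendar time is not a patient characteristic, a provider characteristic or a site. The case for naming it comes from a period change that the article itself reports.

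A second reply is that confounding is not shown. This stands in full. The Limitations section reports fewer trauma cases. It does not report faster care or lower mortality. Fewer trauma cases during a pandemic need not mean a less loaded hospital or ambulance service, so even the direction is unknown. The figure of 50% is a maximum, and the article does not say how much of the main phase was affected.

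A reader might infer a large bias in favour of early CRI. For example, put one third of patients in the low-caseload period, with early CRI at 45% versus 22.5% and mortality at 8% versus 11%. The early group's mortality is then 9.5% and the others' 10.2%, a spurious HR of 0.93. The arithmetic is right, but the documents do not support the inputs. At half the usual caseload, supplying one third of patients takes half of the enrolment time: 0.5t/(0.5t + 1 − t) = 1/3 gives t = 0.5, or about 18 of the 36 main-phase months at the maximum reduction. Early CRI must also double. If only a pilot-sized share were affected (1,000 of 15,400, or 6.5%), contrasts of the same size would give about 0.98.

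**Conclusion.** This is a minor but worthwhile improvement, not a demonstrated error. The stated adjustment leaves out calendar time, although the article reports a caseload change of up to half at the start of enrolment and treats time trends in care as something to study. Under moderate assumptions the resulting bias is about 0.97 to 1.035 on the ratio scale, in either direction, and about 0.99 to 1.01 if early CRI differs by 5 points. That is small against the targeted 15% reduction, though at the extremes it is more than half a standard error.

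Two stronger readings should be avoided: that period is an established confounder, and that the bias is known to favour early CRI. The documents give no data on how CRI timing or mortality changed over enrolment. The sizes above rest entirely on the assumed ranges and on the plan's own 14,400 patients, 30% early CRI and 10% mortality.

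**What to change.** Add calendar time of injury, by quarter or as a smooth term, to the multivariable mortality and morbidity models. Alternatively, stratify the Cox baseline hazard by calendar period. Report the CRI effect with and without the term, so that readers can see whether period matters. Extend the Limitations section to say that period may confound the CRI associations as well as lower the reported rates. If the full analysis plan already has such a term, naming it in the article is enough.

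The cost is small. The injury date comes from data already collected. Quarters over 36 months use 12 − 1 = 11 degrees of freedom against about 1,440 expected deaths, and a smooth term uses fewer. For the two-level period examined here, the loss is at most about one point of power (80.7% to 79.8%). A finer term could explain slightly more of the exposure, and the same formula gives its cost.
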